## Abstract

**Purpose:**

The purpose of this study is to summarize the design and methodology of a large-scale trial in northern China, the Beijing Angle Closure Progression Study (BAPS). This trial is designed to explore the 5-year incidence of primary angle-closure suspect (PACS) progressing to primary angle-closure (PAC) or primary angle-closure glaucoma (PACG) and to determine the possible risk factors of disease progression.

**Methods/design:**

The BAPS is a clinic-based, multicenter, noninterventional trial conducted on a sample of urban Chinese adults. Consecutive eligible patients who meet PACS diagnostic criteria will be recruited from eight participating centers, with the trial commencing on August 4, 2022. The target sample size is set at 825 subjects, with follow up planned for a minimum period of 5 years. Baseline examination will include presenting visual acuity, best corrected visual acuity, intraocular pressure (IOP), undilated slit-lamp biomicroscopy, stereoscopic evaluation of the optic disc, visual field test, optical coherence tomography evaluation of retinal nerve fiber layer, ultrasound biomicroscopy and IOLMaster. Questionnaires will also be used to collect detailed personal history. Patients are scheduled to visit the glaucoma clinic every 12 months and may visit the emergency room in case of acute attack of angle closure. Study endpoints include acute PAC episodes, elevated IOP, peripheral anterior synechiae, glaucomatous visual field defect, or glaucomatous abnormality of optic nerve.

**Discussion:**

The BAPS will provide data on the 5-year incidence of PACS progressing to PAC or PACG and determine the risk factors for disease progression. This study will also help redefine high-risk patients with PACS.

## Introduction

Although the global prevalence of primary angle-closure glaucoma (PACG) is less than half that of primary open-angle glaucoma, it poses a significantly higher risk of causing severe bilateral blindness, with rate three times greater than primary open-angle glaucoma (1). PACG is a leading cause of irreversible blindness worldwide (2), characterized by the closure of the anterior chamber angle. Primary angle-closure suspect (PACS), the earliest stage of primary angle-closure diseases (PACD), is defined as 6 or more clock hours of appositional contact between the peripheral iris and posterior trabecular meshwork on gonioscopy. Progression from PACS to primary angle-closure (PAC) involves elevated intraocular pressure (IOP) or the presence of peripheral anterior synechiae (PAS), while PACG involves these features along with glaucomatous optic neuropathy or glaucomatous visual field defects (3). It is estimated that by 2040, the number of PACG cases worldwide is projected to reach 32 million, with a significant proportion occurring in Asia (4, 5). Therefore, a better understanding of the natural history of PACD may play an important role in preventing devastating visual impairment.

Previous studies have reported the prevalence of PAC and PACG ranging from 1 to 11.3% (6–9). However, longitudinal data on the incidence and progression of earlier stages of angle closure that precede PAC/PACG are scarce, particularly in Asian population (10–14). For instance, a Danish study demonstrated that the rate of progression from the condition of shallow anterior chamber to PACG was 16% over 10 years (15). In Asia, PACS progression rates to PAC or PACG range from 5.3 to 25.5% (10–14). Identified risk factors for progression include bilateral PACS (10), smaller angle width (11), shorter angle open distance, flatter iris curvature, and older age (12).

Most studies assessing anterior chamber characteristics have utilized examinations like IOLMaster, A-scan, and anterior segment-optical coherence tomography (AS-OCT). However, the ultrasound biomicroscopy (UBM) has not been widely used, despite its valuable role in evaluating angle closure. UBM can provide detailed information on the volume of the ciliary body, the degree of ciliary anterior rotation, and parameters related to the vitreous zonule (VZ), which are often overlooked (16). Historically, laser peripheral iridotomy (LPI) was considered to be a precaution against progression of PACD, but recent studies postulated that the benefit of prophylactic LPI was limited for PACS (17). Therefore, identifying PACS patients with high progression risks accurately is imperative to apply LPI selectively.

The Beijing Angle Closure Progression Study (BAPS) aims to explore the 5-year incidence of PACS progressing to PAC or PACG and identify potential risk factors for disease progression. This study seeks to provide evidence for developing accurate management strategies for PACS.

## Materials and methods

### Study design and principal aims

The BAPS is a clinic-based, multicenter, noninterventional trial conducted on a sample of urban Chinese adults. This study has been approved by the ethics committee of Peking University People’s Hospital and will adhere to the tenets of the Declaration of Helsinki. The protocol is prospectively registered at www.cilinicaltrials.gov (registration number NCT05563623). Institutional Review Board/Ethics Committee approval has been obtained.

The comprehensive study protocol is summarized in Table 1, providing an overview of the study design and key steps.

**Table 1 tab1:** Comprehensive study protocol for the Beijing angle closure progression study.

Step	Description	Details
Study design	Clinic-based multicenter noninterventional trial	Conducted on a sample of urban Chinese adults
Ethics approval	Approved by the Ethics Committee	Peking University People’s Hospital, follows the Declaration of Helsinki
Registration	Protocol registered	www.clinicaltrials.gov (NCT05563623)
Participant recruitment	Recruitment centers	8 participating centers
Inclusion criteria	Criteria for eligibility	6 or more clock hours of angle circumference with no PAS and normal IOP Aged 40–75 years Provide informed consent
Exclusion criteria	Criteria for exclusion	Evidence of PAC or PACG Previous intraocular surgery or laser treatment Severe health problems
Baseline examination	Comprehensive initial examination	Visual acuity IOP measurement Slit-lamp biomicroscopy Gonioscopy OCT UBM
Follow-up visits	Regular follow-up schedule	Every 12 months, including examinations for IOP, visual acuity, gonioscopy, UBM, OCT, and visual field testing
Study endpoints	Criteria for study endpoint	Acute PAC episode Elevated IOP (>21 mmHg) Presence of PAS Glaucomatous visual field defects
Data management	Handling and storing data	Non-image data in BAPS Database Image/original data stored securely Privacy of participants protected
Statistical analysis	Data analysis methods	SPSS 22.0 for analysis Significance level: 0.05 Independent *t*-test, Mann–Whitney U test, Pearson chi-square test, logistic regression analysis, Cox regression analysis

IOP, intraocular pressure; PAS, peripheral anterior synechiae; PAC, primary angle-closure; PACG, primary angle-closure glaucoma; OCT, optical coherence tomography; UBM, ultrasound biomicroscopy; BAPS, Beijing angle closure progression study.

Consecutive eligible patients will be recruited from 8 participating centers, with the trial commencing on August 4th, 2022. Patients who agree to participate will undergo a comprehensive baseline examination, while those who decline will be asked to provide a reason. Both verbal and written informed consent will be obtained from every patient (Figure 1).

**Figure 1 fig1:**
[figure not shown]
Outline of the workflow for screening and enrollment in the BAPS.

The principal aim of this trial is to explore the 5-year incidence of PACS progressing to PAC or PACG and to determine the risk factors for disease progression.

### Sample size estimation

Currently, many studies have reported the prevalence of PACS in the population, with rates ranging from 4.68% (95% Confidence Interval [CI]: 4.541–4.819%) to 10.4% (95% CI: 9.6–11.2%) (7–9, 18–21). However, few studies have investigated the incidence of PACS progressing to PAC or PACG (11, 12, 15, 22, 23). In a population-based prospective study conducted in India, 11 out of 50 PACS eyes (22%; 95% CI: 9.8–34.2%) developed PAC over 5 years (23). Another follow-up study in Denmark involving 75 PACS eyes reported a progression incidence of 16% (15). Given the similarity between our sample characteristics and those in the Indian study, we conservatively estimated the incidence of PACS progressing to PAC or PACG at 20%. To analyze the risk factors, we plan to collect a larger sample size than previous studies. Considering the number of candidate risk factors and the prevalence of PACS, we will use standard sample size calculation formulas for proportions, aiming for a desired level of statistical power of 80% and a significance level of 0.05. Based on these calculations, we estimate that 700 subjects are needed to achieve reliable results. Accounting for an anticipated attrition rate of up to 15%, we set the final sample size at 825 individuals, expecting to have complete follow-up data for 700 individuals at the end of the study.

### Clinical data collection

All subjects will be screened through a preliminary survey to verify their eligibility for recruitment in this trial. A comprehensive baseline examination will be conducted for every enrolled subject. Patients will be monitored for 5 years. All examinations involving subjective judgment and manipulation, such as Goldmann applanation (GAT), UBM, and gonioscopy, will be performed by experienced examiners.

For the analysis, we will enroll only one eye per subject to avoid correlation issues between eyes of the same individual. The selection of which eye to include will be randomized to ensure that there is no selection bias.

Inclusion criteria are as follows: (1) Static gonioscopy identifying six or more clock hours of angle circumference in which the posterior (usually pigmented) trabecular meshwork is not visible in both eyes with no PAS, and normal IOP, optic nerve, and visual field; (2) Patients aged between 40 and 75 years; and (3) Patients capable of providing informed consent.

Exclusion criteria are as follows: (1) Any evidence of PAC, characterized by a narrow angle as defined above, but with PAS and/or IOP > 21 mmHg, or PACG, indicated by a visual field defect or glaucomatous optic neuropathy; (2) Previous intraocular surgery or laser treatment, including cataract surgery, laser trabeculoplasty, trabeculectomy, laser peripheral iridectomy, and laser iridoplasty; (3) Signs of prior acute attack, such as glaucomatous fleck, keratic precipitates, or iris atrophy; (4) Anterior segment structural abnormalities, such as iris or ciliary body tumor; (5) Severe health problems that preclude follow-up, such as end-stage heart disease, kidney disease, lung disease, or terminal cancer; (6) Severe eye diseases requiring treatment, such as cataract, macular disease, and retinal detachment; and (7) Patients who plan to move from the area within the next 5 years.

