Optical coherence tomography (Spectralis HRA + OCT, Heidelberg Engineering GmbH, Heidelberg, Germany) will be employed to assess retinal nerve fiber layer (RNFL) defects. The visual field (VF) will be evaluated using the Swedish Interactive Threshold Algorithm (SITA) program 24-2 on a Humphrey Field Analyzer (Carl Zeiss Meditec, Inc., Dublin, CA) to identify characteristic glaucomatous VF defect. A characteristic glaucomatous defect is defined as a visual field abnormality consistent with the pattern of optic nerve damage caused by glaucoma (3).

UBM (Aviso, Quantel Medical, Inc., Bozeman, MT) measurements will be conducted using a 50-MHz transducer by well-trained operators blind to the clinical data. All patients will undergo UBM imaging in a supine position under room light [illumination 120 lux, measured with a luminance meter (Model ST-92, Beijing Teachers University Photoelectricity Instrument Factory, Beijing, China)]. After topical anesthesia with oxybuprocaine eye drops, an eyecup containing normal saline will be carefully mounted on the globe. The UBM transducer will be moved perpendicularly over the ocular structures without exerting pressure on the globe or touching the cornea. Measurements will be taken from both eyes in the superior, inferior, temporal, and nasal quadrants, as well as nasal-temporal scans centered on the pupil to obtain a full view of the anterior segment. During dynamic scanning, if the VZ appears on the monitor, the image will be stored. The strand attaching to the posterior VZ insertion zone and posterior lens equator, referred to as PVZ INS-LE, will also be categorized as VZ. All images will be acquired under consistent room lighting condition. Only images with a clear view of the scleral spur, angle, ciliary body, iris, and anterior surface of the lens will be included in the analysis.

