### Study endpoint and termination of follow-up (censored data)

The study endpoint will be reached if the participant meets any of the following criteria: (1) An episode of acute PAC; (2) Any PAS; (3) IOP > 21 mmHg; (4) Any patchy TM pigmentation; and (5) Glaucomatous visual field defect, RNFL defects, or glaucomatous abnormality of optic nerve. Participants meeting at least one of the five criteria will be classified in the progression group. For patients experiencing an acute angle-closure attack, the time of progression will be recorded accurately. If chronic progression (PAS or glaucomatous abnormality of optic nerve) is detected during routine follow-up, the progression time will be recorded based on the follow-up time.

The following conditions will be considered reasons for termination of follow-up and will be defined as censored data: (1) Inability to continue follow-up for various reasons, such as severe systemic diseases or relocation; (2) Development of new severe ocular diseases requiring treatment, such as vision-threatened cataract, retinal detachment, or age-related macular degeneration; (3) Missing 3 out of 6 monthly follow-up visits; and (4) Requesting withdrawal of informed consent.

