### Statistical analysis plan

All parameters measured in UBM will be calculated by averaging the corresponding measurements from both horizontal and vertical images. The normality of the data will be evaluated by using the Shapiro–Wilk test. Means and standard deviations will be calculated for all continuous variables. Baseline characteristics will be compared between progression group and non-progression group using the independent *t*-test or Mann–Whitney U test for continuous variables and the Pearson chi-square test for categorical variables.

The primary outcome is the progression rate, in other words, the rate of acute PAC (IOP > 21 mmHg) and the proportion of eyes developing PAS. We will evaluate the risk factors for PACS progression to PAC or PACG using univariable and multivariable logistic regression analysis, as well as Cox regression analysis. All statistical analyses will be performed using the software SPSS 22.0 (SPSS, Inc., Chicago, IL) with a significance level set at 0.05.

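### The primary endpoint has no single unit: one random eye is analysed, but progression is assigned to the participant on any criterion, without limiting it to that eye

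*Protocol article*

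**What the plan says.** Four sections of the protocol article bear on the unit.

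- **Clinical data collection.** The angle finding is required bilaterally: "trabecular meshwork is not visible in both eyes with no PAS, and normal IOP, optic nerve, and visual field". Every participant therefore enters with two eyes at risk. The analysis keeps one: "For the analysis, we will enroll only one eye per subject to avoid correlation issues between eyes of the same individual". The choice is random: "The selection of which eye to include will be randomized to ensure that there is no selection bias".
- **Study endpoint and termination of follow-up.** The event belongs to the person: "The study endpoint will be reached if the participant meets any of the following criteria". So does the grouping: "Participants meeting at least one of the five criteria will be classified in the progression group". Neither sentence mentions the study eye.
- **Statistical analysis plan.** The primary outcome is "the rate of acute PAC (IOP > 21 mmHg) and the proportion of eyes developing PAS". Its second part counts eyes; its first part has no stated unit. Baseline characteristics are then compared between the progression and non-progression groups, and risk factors go into logistic and Cox models.
- **Sample size estimation.** The 20% planning rate is drawn from eye-level reports (11 of 50 eyes, and 16% of 75 eyes) and applied to a count of subjects. The Discussion gives the same 22% and confidence interval as a share of patients.

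In Ophthalmologic examinations, UBM is explicitly bilateral: "Measurements will be taken from both eyes in the superior, inferior, temporal, and nasal quadrants". No section says how an event in the fellow eye alone is classified, or which eye's measurements then enter the models.

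**The concern.** The principal aim is a 5-year incidence together with its risk factors. With two eyes at risk per person, risk per eye and risk per person are different quantities, and the text supports either.

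If the endpoint section is applied as written, a participant whose unselected eye develops synechiae joins the progression group, while the angle, iris and ciliary measurements on file for the analysis come from the eye that did not progress. Person-level factors such as age are unaffected. Eye-level factors would tend to look weaker than they are, and these are the reason UBM was added to the study. If instead only study-eye events count, there is no mismatch, but fellow-eye events go unused. Leaving the choice open also allows it to be made after the results are known.

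**Working it through.** **The plan's own figure.** 700 / (1 − 0.15) = 823.5, so 824, against the stated 825; 825 × 0.85 = 701. The enrolment target reproduces. The 700 cannot be re-derived because no detectable effect is stated; that is a separate matter and plays no part here.

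**Inputs.** Risk per eye p = 0.20 (Sample size estimation, read per eye as its sources are). 700 evaluable subjects (same section). Two eyes at risk per subject (inclusion criteria). The inter-eye correlation ρ of the progression outcome is given nowhere; 0.2 to 0.9 is an assumption.

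**Formulas.**
- Both eyes progress: P(both) = p² + ρp(1−p) = 0.04 + 0.16ρ
- Either eye progresses: P(either) = 2p − P(both)
- Fellow eye only: p − P(both) = p(1−p)(1−ρ) = 0.16(1−ρ). This is also the gap between the two incidences.
- Effective eyes if both are analysed: 1400/(1+ρ). Share of information lost with one eye: 1 − 700(1+ρ)/1400 = (1−ρ)/2.

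**Literal participant-level reading** (the study-eye reading gives 20%, or 140 events, throughout):

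| ρ (assumed) | P(both) | Incidence per person | Gap, points | Progressed, of 700 | Fellow eye only | Share of progression group |
|---|---|---|---|---|---|---|
| 0.2 | 7.2% | 32.8% | 12.8 | 229.6 | 89.6 | 39.0% |
| 0.4 | 10.4% | 29.6% | 9.6 | 207.2 | 67.2 | 32.4% |
| 0.6 | 13.6% | 26.4% | 6.4 | 184.8 | 44.8 | 24.2% |
| 0.9 | 18.4% | 21.6% | 1.6 | 151.2 | 11.2 | 7.4% |

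**Against sampling error.** The 95% half-width for 20% in 700 eyes is 1.96 × √(0.16/700) = 2.96 points. The gap 16(1−ρ) points exceeds it whenever ρ < 1 − 2.96/16 = 0.815. Below that, the choice of unit moves the headline by more than the half-width.

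**The converse.** If 20% were the risk per person, the risk per eye would be 12.4%, 14.0%, 16.0% or 18.5% at ρ = 0.3, 0.5, 0.7 or 0.9.

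**Study-eye reading: cost in precision.**

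| ρ (assumed) | Effective eyes, both analysed | Information lost with one eye | Half-width with both eyes, points |
|---|---|---|---|
| 0.2 | 1,167 | 40% | 2.30 |
| 0.4 | 1,000 | 30% | 2.48 |
| 0.6 | 875 | 20% | 2.65 |
| 0.9 | 737 | 5% | 2.89 |

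These gains apply to the incidence estimate. For an eye-level risk factor the gain also depends on how strongly that measurement is correlated between eyes, which the documents do not give. For the same reason the weakening of risk factors under the literal reading cannot be quantified.

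**The case against.** The strongest reply is that Clinical data collection already fixes the unit. With one eye per subject, participant and analysed eye correspond one to one. The endpoint section's participants, the statistical section's eyes and the use of eye-level rates to size a number of subjects can then share one denominator. A condensed article may also leave the handling of fellow-eye events to the full protocol. This is a coherent reading and may be the intended one. It does not settle the matter, because the endpoint section states a rule rather than staying silent, and that rule, as worded, admits events in either eye.

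The other side is right on several further points.

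- A reader might infer that fellow-eye events will be paired with the wrong eye's measurements. The documents do not say so; it follows only if the endpoint rule is applied literally with study-eye covariates.
- A reader might infer that using one eye is an error, or that half the information is thrown away. One randomly chosen eye per subject is a valid way to avoid inter-eye correlation. Half the eyes are left out, but the information lost is (1−ρ)/2, which reaches one half only when the eyes are independent.
- At ρ = 0.9 the two incidences differ by only 1.6 points and the gain from the second eye is about 5% (737 against 700).
- Bilateral collection is explicit only for UBM. The Follow-up visits section does not state laterality.

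**Conclusion.** The concern holds as an inconsistency in the unit of the primary endpoint. Two rules in the text give different primary results. At 20% risk per eye, incidence is 20% on the study-eye rule and between 32.8% (ρ = 0.2) and 21.6% (ρ = 0.9) on the participant rule. Fellow-eye-only events would then make up about 39% to 7% of the progression group, with biometry from an eye that did not progress. The size rests on an assumed correlation and on reading the 20% as a rate per eye; the inconsistency rests on neither. If only study-eye events are meant, the planned analysis is valid and the remaining issue is precision, 40% to 5% of the available information. It should be corrected before outcomes are examined, but it does not invalidate the design.

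**What to change.** 1. Define the endpoint per eye in the endpoint section and in the statistical analysis plan, so that an eye's outcome is always paired with that eye's own baseline measurements. State how an event in the fellow eye alone is classified.
2. Report incidence per eye and per person (either eye) separately, each labelled with its unit, and say which of the two the 20% planning rate refers to.
3. Where both eyes have data, analyse both in a Cox or GEE model with participant-clustered robust variance, and keep the planned random-eye analysis alongside it.

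Steps 1 and 2 cost mainly wording, although either-eye incidence needs the endpoint criteria assessed in both eyes at follow-up, which the article should confirm. Step 3 needs clustered-variance software and measurement of the second eye's stored UBM images. That is real work: caliper measurements of many parameters in four quadrants, for up to 825 further eyes, with observer-agreement repeats if these are extended to them. If this is not affordable, steps 1 and 2 alone remove the inconsistency.

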Alsbirk et al. conducted a study on angle closure in the population of Greenland Eskimos, who exhibited a high incidence of PACG, similar to conditions observed in Southeast Asian populations (15). The study reported that at a 10-year follow-up, 16% (95% CI, 8.5–26.3%) of 75 eyes with PACS progressed to the equivalent of ISGEO PAC (synechial PAC) or PACG (acute or chronic). Slit-lamp screening (LACD and ACD) was effective in identifying a subgroup at risk for developing PACG over the 10-year follow-up (15). However, the study has two significant limitations. First, the use of slit lamp alone to assess LACD and ACD is subjective and unreliable. Second, the study did not use the ISGEO classification, as it was conducted earlier and applied previous diagnostic criteria (35). Consequently, it cannot provide valuable guidance for the treatment of PACD. Wishart and Batterbury’s study reported that 36% of patients in the narrow angle group developed PACG over an average 4-year follow-up period (36). This study faced similar issues as Alsbirk et al.’s study, and it was not observational, as it employed IOP-lowering medications for patients. Therefore, it could not provide valuable insights into the natural history of PACD.

An Indian prospective study demonstrated that 22% (95% CI, 9.8–34.2%) of patients with PACS developed PAC, but no PACG were observed during the 5-year follow-up. The study identified bilateral PACS as a clinical risk for disease progression, but no biometric characteristics were found to be significant (10). The sample size in this study was relatively small, with only 50 PACS were examined, and the participants were not consecutively enrolled. Instead, the patients previously diagnosed as PACS in other studies were invited for a review examination. Consequently, the incidence of disease progression may be biased. Additionally, the absence of PACS cases progressing to PACG over the 5-years period is inconsistent with clinical experience.

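### Only patients with PACS in both eyes can enrol, but the aim, primary outcome and conclusion are worded for PACS in general, so the incidence should be labelled as that of bilateral PACS

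*Protocol article*

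**What the plan says.** Criterion 1 in *Clinical data collection* requires that the "trabecular meshwork is not visible in both eyes with no PAS, and normal IOP, optic nerve, and visual field". The same section has one randomly chosen eye per patient analysed.

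Elsewhere laterality is not mentioned. The *Introduction* defines PACS as "6 or more clock hours of appositional contact between the peripheral iris and posterior trabecular meshwork on gonioscopy". In *Study design and principal aims*, the text below Figure 1 reads "The principal aim of this trial is to explore the 5-year incidence of PACS progressing to PAC or PACG". The entry in Table 1 is "6 or more clock hours of angle circumference with no PAS and normal IOP". The primary outcome (*Statistical analysis plan*) and the *Conclusion* also refer to progression without limiting it to bilateral cases.

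The *Introduction* lists bilateral PACS first among identified risk factors for progression. The *Discussion* says of the Indian 5-year study: "The study identified bilateral PACS as a clinical risk for disease progression, but no biometric characteristics were found to be significant". *Sample size estimation* takes its 20% planning rate from that study with the words "Given the similarity between our sample characteristics and those in the Indian study".

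**The concern.** The principal aim is descriptive: an incidence in a named population. For such an aim, the population that can enrol has to be the population named in the result. Here a unilateral suspect who meets the article's definition of PACS is excluded, and no section acknowledges or explains this.

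The restricting feature is one that the article itself links to faster progression. Reported without qualification as the 5-year incidence of PACS, the result would come from a subgroup expected to progress more often. It would then be set beside the earlier Asian progression rates of 5.3 to 25.5% that the *Introduction* quotes for PACS. The hope of redefining high-risk PACS is affected as well: bilaterality does not vary in this cohort, so the study can say nothing about unilateral suspects or about bilaterality as a predictor.

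**Working it through.** **1. The plan's own figures.** Inputs from *Sample size estimation*: 700 evaluable subjects, 15% attrition, 20% incidence.
- 700 / (1 − 0.15) = 823.5, rounded up to 824, against 825 stated. This reproduces within rounding.
- Expected events: 700 × 0.20 = 140.
- Source rate: 11 / 50 = 22%.

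The arithmetic is not in question. What is in question is the population to which the 20% belongs.

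**2. The passages side by side.**

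| Place | Population |
|---|---|
| Inclusion criterion 1 | angle finding in both eyes |
| Random choice of study eye | works without adaptation only if either eye qualifies |
| Definition, principal aim, primary outcome, conclusion | no laterality stated |
| Table 1 | no laterality stated (condensed summary) |

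The eye-selection rule supports the plain reading of criterion 1 as bilateral PACS.

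**3. The source of the planning rate.** A study can identify bilaterality as a risk factor only if bilaterality varied in it, so the Indian cohort held both unilateral and bilateral cases. It was population-based (*Sample size estimation*) and not consecutively enrolled (*Discussion*). BAPS is clinic-based, consecutive and bilateral only. The two sections cite the Indian study under different reference numbers, but the 22%, the interval of 9.8–34.2%, the 50 PACS and the 5 years are identical, so they describe the same data.

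**4. Possible size, by assumption only.** The documents give neither the share of bilateral cases nor a risk ratio. Let b be the bilateral share, u = 1 − b the unilateral share, and RR the bilateral-to-unilateral risk ratio.

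*If 20% is the rate in a mixed cohort:* unilateral rate = 0.20 / (b × RR + 1 − b), and bilateral rate = RR × unilateral rate.
- b = 0.9, RR = 2: 0.20 / 1.9 = 10.5%, so bilateral 21.1%.
- b = 0.5, RR = 2: 0.20 / 1.5 = 13.3%, so bilateral 26.7%.
- Over b = 0.3 to 0.9 and RR = 1.5 to 4, the bilateral rate runs from 20.7% to 42.1%, or about 145 to 295 events in 700, against 140 planned.

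*If 20% is the rate in bilateral PACS:* overall rate = (1 − u) × 20% + u × 20% / RR.
- u = 0.2, RR = 1.5: 16.0 + 2.7 = 18.7%, a difference of 1.3 points.
- u = 0.3, RR = 2: 14.0 + 3.0 = 17.0%, a difference of 3.0 points.
- u = 0.4, RR = 3: 12.0 + 2.7 = 14.7%, a difference of 5.3 points.

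For scale, a 95% interval at 20% and n = 700 has half-width 1.96 × √(0.2 × 0.8 / 700) = 2.96 points. This is my calculation; the article states no interval width.

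**The case against.** The restriction is stated openly in the full inclusion list, where readers look for it. An aim commonly names the disease and leaves the exact population to the eligibility criteria. Bilateral enrolment also makes the random choice of eye workable. All of this is fair: restricting to bilateral PACS is a legitimate design choice. What it does not answer is that the conclusion is still worded for all PACS, on a feature that the article reports as prognostic.

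Several stronger readings are tempting but not supported:
- *Table 1 contradicts criterion 1.* It is a summary that also drops other listed criteria, such as a normal visual field and signs of a prior acute attack. Its silence is condensation.
- *The incidence will certainly be too high, by more than its confidence interval.* Within the article, the risk-factor evidence is one study with 11 events among 50 PACS, which the *Discussion* itself calls small and possibly biased in its incidence. No effect size is given. Of the three scenarios built on a 20% bilateral rate, one difference lies well inside the computed half-width, one about equals it, and only the most extreme clearly exceeds it.
- *The sample size is undermined.* A higher rate gives more events, not fewer.
- *The risk-factor analysis is confounded because bilaterality cannot be adjusted for.* A factor held constant by restriction cannot confound the other predictors. The loss is in generalisability.

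One may also say that the similarity sentence does not specify which characteristics are meant. That is true, so the claim need not fail in every respect, but it does not hold on laterality or on setting.

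**Conclusion.** The point holds as a mismatch between the enrolled and the named population. As planned, BAPS estimates the 5-year incidence in clinic patients with bilateral PACS. On the article's own, limited evidence, that rate is expected to exceed the rate for PACS overall. The direction rests on one small study, and the size cannot be derived from the documents. The illustrative differences run from about 1 point, when nearly all source cases are bilateral or the risk ratio is modest, to several points otherwise, and depend entirely on the assumed share and risk ratio. The similarity offered for the 20% planning rate does not hold on laterality or setting, though planning is not endangered by this. Neither the internal validity of the risk-factor analysis nor the enrolment target is in doubt. What needs correcting is the population to which the results are said to apply.

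**What to change.** Keep criterion 1 and the random choice of eye. Then:
- State the target population as bilateral PACS in the aim, Table 1, the primary outcome and the conclusion.
- Limit the incidence and risk-factor conclusions to bilateral PACS, and make the difference in laterality explicit in any comparison with earlier studies.
- In *Sample size estimation*, replace the claim of similar samples with a statement that 20% is an assumption taken from a population-based cohort of mixed laterality.

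These are wording changes and need no new data or examinations. The cost is a narrower conclusion that does not extend to unilateral suspects. Opening enrolment to unilateral cases part-way is not recommended here: it would mix two populations and break the present eye-selection rule.
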